#### Chemotherapy-related toxicities

To assess the effect of IF on chemotherapy-related toxicities (hematological and non-hematological toxicities), the incidence and severity of treatment-related adverse events (AEs) will be recorded by the Common Terminology Criteria for Adverse Events (CTCAE, v5.0). Laboratory measures focused on hematological toxicities, renal and liver functions as well as specific biomarkers for metabolism and tumor immunology (see **Table 1**) will be analyzed during the whole study period.

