## Methods

### Study design and setting

This study is designed as a prospective, two-arm parallel-group, multi-center, open-label, randomized-controlled clinical trial (phase III trial). It will be conducted at the Department of Gynecology and Obstetrics of the University Medical Centre of the Johannes Gutenberg University Mainz, Germany, as well as the department of Gynecology and Obstetrics at the St. Josef’s Hospital, Wiesbaden, Germany. All data will be recorded pseudonymized. Only the principle investigator of the study, as well as the study nurses in charge will have access to the pseudonymization list in case of adverse events or trial termination.

The active fasting period will be conducted for three months during CHT. Participants will be scheduled for study visits during their routine care (d1 of each cycle) and routine laboratory visits on days 8 (and 15 in three week cycles) of each cycle during the three months of the active trial period. Additional study visits will be scheduled for nutritional counseling prior to the start of the chemotherapy as well as a follow up visit at six months (**Table 1**). QoL including fatigue assessment will be performed at baseline, each week during the 12 weeks active trial period as well as at the six months follow-up. Specific quality of life aspects regarding sleep quality and pelvic floor function will only be assessed at baseline, after three months and after six months.

**Table 1 T1:** Visit overview and outcome measures assessed during each study visit.

Timepoint	Study period						
	t_-1_ *(3d - 4w prior to CHT)*	All cycles d_1_	All cycles d8	3-week cycles day 15	12 weeks after Start CHT ( ± 1 week)	Post surgery where applicable	6 months follow up ( ± 2 weeks)
Enrolment Eligibility screen Informed consent Randomization Allocation	XXXX						
Interventions Intermittent fasting Normal diet Nutritional counselling	XXX				→ →		Voluntary continuation of IFSwitch to IF possible
Assessments Demographics Medical history Current medication Anthropometric measurements Vital signs Physical examination CTCAE Hematogram Glucose/ketone levels Organ Blood panely-H2AX DNA damage essayImmunological responseTumor response Tumor markers Pathological response Radiological response	XXXXXXXXXXX(X)^3^	XXXXXXXXX^1^	XX^2^	X	XXXXXXXXX(X)	X	XXXXXXXX(X)

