#### Body weight changes and safety

To assess the safety of IF during CHT, during which many patients struggle to maintain their weight, changes in BMI will be recorded and compared between groups. Furthermore, regular laboratory assessments of blood values such as hematograms, liver and kidney function will be assessed over the study period. A detailed overview of laboratory values assessed can be found in **Appendix A**. Laboratory values will be accepted if obtained ± 1 day of the planned assessment day (e.g. one day prior to CHT).

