### Statistical analysis

Patients will be randomized to the intervention or control group (1:1) stratified by tumor entity and study site. The primary endpoint, the difference of the mean change of fatigue over a period of three months as measured by the FACIT-FS© score, will be compared between both groups using mixed models. Confounders such as age, type of CHT, neoadjuvant/adjuvant vs metastatic treatment, the Eastern Cooperative Oncology Group performance status (ECOG), histological tumor grade, and Fédération Internationale de gynécologie et d’Obstetrique (FIGO) -stage will be included in the mixed models. Laboratory data, as well as QoL questionnaire-based outcomes will also be assessed using mixed models. Missing data for the primary outcome as well as secondary outcomes with the potential to become main outcomes in subsequent larger trials will be imputed. Where possible, missing questions from FACT^©^ questionnaires will be prorated using the average of the other answers in the subscale (prorated subscale score = [sum of the item scores]*[N of items in subscale]/[N of items answered]) as long as more than 50% of the items are answered. Data will be imputed by drawing values from the distribution of the control group (jump to reference).

A comprehensive summary will be given for primary and secondary endpoints, including absolute and relative frequencies for categorical and binary variables as well as mean and standard deviation or median and interquartile range and minimum-maximum for all data with at least interval scale level. Pathological response rates after neoadjuvant CHT will be compared using the Chi square test. Radiological response rates (complete response, partial response, stable disease, and progressive disease) will be compared between the arms at 3 months and 6 months using the Mann-Whitney-U-tests. The occurrence of any adverse event as well as the occurrence of grade 3 or higher adverse events will be compared between both groups using the Chi square test. And a list of immunological and metabolic parameters will be compared between both groups using the Mann-Whitney-U test. A paired Wilcoxon test will be used to compare the change in BMI over three months between both groups.

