### Data monitoring, interim analysis and trial termination

Data will be collected on a personalized case report form at the predefined time points depicted in **Table 1**. Data will be entered in a protected database (RedCap). Only authorized members of the IFAST study team will be allowed to enter, store and access participant data. Paper-based data will be stored at the department of obstetrics and women’s health at the University Medical Center Mainz. Clinical routine data assessments will be stored in the respective patient’s clinical files at the University Medical Center Mainz and St. Josef’s Hospital.

The safety of IF has been proven in many smaller studies, including our pilot trial (9) for healthy people as well as patients under chemotherapy (25). No severe adverse events were observed; thus, no interim analysis is planned. The trial can be terminated by the patient at any time without the risk of negative consequences by withdrawing consent. The discontinuation of the intervention can be decided upon by the investigator due to medical reasons, including the reduction of the BMI to <18 kg/m^2^, acute severe CHT induced side-effects requiring hospitalization or acute, severe non-chemotherapy related medical illnesses requiring hospitalization. Patients terminating the intervention will be asked to fill out the questionnaires outside of the study protocol.

A data monitoring committee consisting of a medical doctor and a study nurse will be overseeing the study visit schedules. All investigators will be obliged to report any changes or deviations of the protocol to the data monitoring committee. Any serious adverse events will be reported to the data monitoring committee and discussed with the principal investigator within 48 hours of occurrence. The termination of the trial for the participant can be decided upon based on the criteria mentioned above by the principal investigator. The termination of the whole trial can be determined by the principal investigator together with the data monitoring committee due to unexpected serious adverse events based on the intervention or due to failure to recruit the planned number of patients.

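### Adverse events are recorded if treatment-related but compared as any adverse event, so in this open-label trial an attribution made with the arm known can decide which non-serious, non-laboratory events count

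*Protocol article*

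**What the plan says.** Under Chemotherapy-related toxicities, the protocol article says that "the incidence and severity of treatment-related adverse events (AEs) will be recorded", using CTCAE v5.0. It is the article's only statement of which non-serious adverse events are collected. It does not say whether treatment means chemotherapy, fasting or both.

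Under Statistical analysis: "The occurrence of any adverse event as well as the occurrence of grade 3 or higher adverse events will be compared between both groups", by chi-square test. No relatedness condition is attached.

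Study design and setting describes the trial as open-label. Tumor response describes blinded reading for radiology and unaware pathologists. No similar arrangement is described for adverse events.

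Some safety information is collected without any attribution:
- Data monitoring, interim analysis and trial termination: "Any serious adverse events will be reported to the data monitoring committee and discussed with the principal investigator within 48 hours of occurrence".
- Body weight changes and safety: "changes in BMI will be recorded and compared between groups", and "regular laboratory assessments of blood values such as hematograms, liver and kidney function will be assessed over the study period".
- Table 1 lists CTCAE among the assessments with no restriction.

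**The concern.** CTCAE grades severity. Relatedness is a separate judgement, and here the person making it knows the arm. A control patient with nausea or dizziness has chemotherapy as the obvious trial-related explanation. A fasting patient with the same symptom has two. If treatment is taken to mean chemotherapy, as the section heading suggests, a symptom put down to fasting falls outside the recording rule in one arm, while the same symptom stays inside it in the other.

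Two errors could follow. Equal toxicity could look like a benefit of fasting, and tolerance of chemotherapy is part of the trial's title. A side effect of fasting itself could also drop out of the comparison. The Discussion names headache and increased fatigue as common in the first two weeks of fasting. Fatigue is measured separately by questionnaire, but headache has no other stated route into the safety data.

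**Working it through.** **1. The two rules side by side.**

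| | Recording (Chemotherapy-related toxicities) | Comparison (Statistical analysis) |
|---|---|---|
| Scope | treatment-related events | any event; grade 3 or higher |
| Relatedness condition | yes, with treatment undefined | none |
| Judged blind to arm | not described | – |

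The recorded set is narrower than the compared set, and nothing in the article reconciles them.

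**2. What is exposed.** Take away serious events (reported whatever the cause), BMI, and blood count, liver and kidney values (measured on schedule). What remains is non-serious clinical symptoms such as headache, nausea and dizziness.

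**3. The plan's own figures.** The article gives no adverse event rate and no power for this comparison, so there is none to reproduce. Its sample size concerns fatigue: 2 × (1.960 + 1.282)² × 13.7² / 9.1² = 47.6, so 48 per group, as stated, raised to 55 for drop-out. The point does not depend on this. I use only the 55 per arm.

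**4. Illustration of a false benefit (all rates assumed).** Let the true risk p be equal in both arms, and let a_C and a_F be the shares called treatment-related in control and fasting patients. Recorded risks are p × a_C and p × a_F. The share is applied per patient, as if one event decided each patient's status.

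*Scenario A, grade 3 or higher:* p = 50%, a_C = 95%, a_F = 80%.
- Control: 0.50 × 0.95 = 47.5%. Fasting: 0.50 × 0.80 = 40.0%. The spurious difference is 7.5 points.
- Two-sided pooled test, 55 per arm: rejection in 12.0% of simulated trials and 11.8% by exact enumeration, of which 11.5 points favour fasting. With 95% in both arms, exact enumeration gives 4.5%.

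*Scenario B, a range:* a_C = 90%, a_F = 80% or 70%. The chance of a significant result in favour of fasting is about Φ{[d√n − 1.96√(2p̄(1−p̄))] / √(p₁(1−p₁) + p₂(1−p₂))}, where p₁ and p₂ are the recorded risks, d their difference, p̄ their mean and n = 55. For p = 40% and a_F = 70%, the recorded risks are 36% and 28%: (0.08 × 7.416 − 1.96 × 0.660) / 0.657 = −1.06, so 14%.

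| True rate | Recorded, control | a_F = 80%: recorded; false benefit (approx. / exact) | a_F = 70%: recorded; false benefit (approx. / exact) |
|---|---|---|---|
| 40% | 36% | 32%; 6% / 7% | 28%; 14% / 15% |
| 60% | 54% | 48%; 9% / 8% | 42%; 24% / 23% |
| 80% | 72% | 64%; 14% / 15% | 56%; 42% / 43% |

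Equal attribution gives the nominal 2.5% in that direction.

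**5. Illustration of missed harm (assumed).** Suppose fasting truly adds 20 points, 60% against 40%. With every event recorded, power at 55 per arm is about 54% (exact) to 56% (approximate). If the whole excess is judged unrelated and not recorded, the expected difference is zero.

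**The case against.** A reader might infer that unrelated events are never captured and that the planned comparison cannot be carried out. The article does not support that. The toxicity section describes how one secondary outcome is measured and does not say that other events go unrecorded. Serious events are reported whatever the cause, and Table 1 lists CTCAE without restriction. The two sections could also be read together as any of the recorded treatment-related events. If treatment includes the fasting intervention, events attributed to fasting would be recorded. This is also a condensed article. The full protocol is not shown and may define event collection and causality fields.

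A reader might also extend the concern to the whole toxicity result. That goes too far as well. Weight loss is covered by BMI, and hematological, renal and liver toxicity by scheduled laboratory values. Many grade 3 or higher events would be serious or graded from laboratory values, so the uniform attribution gap in Scenario A is generous. The secondary outcomes are declared exploratory.

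These objections limit the reach of the point but do not remove it. The article states both rules itself, so this is a conflict in the text and not an omitted detail. Serious event reports are described as going to the data monitoring committee, not as feeding the chi-square comparison. Leaving treatment undefined also leaves the direction of any bias open.

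**Conclusion.** The point holds in limited form. The recording rule and the comparison do not match. With open-label assessment and treatment undefined, following the recording rule lets an unblinded relatedness judgement decide which non-serious, non-laboratory events enter the comparison. Serious events, BMI and laboratory values are outside the problem.

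The size is not known. The figures of about 12% rejection in one scenario and roughly 6–43% false benefit across the range rest on assumed true risks, assumed attribution shares applied per patient, and 55 per arm. They also assume that events put down to fasting are left out. A patient with several events would be lost from the count only if all of them were judged unrelated, which would narrow the gap. The article restricts safety to the per-protocol subset, so the numbers analysed may be below 55. That restriction is a separate matter, and correcting it would not bring back events that were not recorded.

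This is an inexpensive improvement worth making before the data are collected. It does not affect the fatigue endpoint.

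**What to change.** Record all CTCAE v5.0 adverse events in both arms regardless of cause. Put relatedness to chemotherapy and relatedness to fasting in two separate fields on the case report form. Base the any-event and grade 3 or higher comparisons on all recorded events, and report related-only events as supportive. Reword the toxicity section to match the Statistical analysis section. If the full protocol already collects all events, only the article's wording needs correcting.

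The cost is a wording change, the relatedness fields, and somewhat more event entry at visits that already take place.

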#### Tumor response

Effects of IF on tumor response between intervention and control group will be compared by tumor specific markers (e.g. CA 125, CA 15-3, CEA, SCC, LDH), pathological response rates after neoadjuvant treatment as well as standardized radiologically evaluation with RECIST 1.1 criteria in metastasized cancers. Imaging will be obtained during routine clinical follow-up and will not be performed specifically for this trial. Radiological responses will be evaluated by a single radiologist blinded to the group allocation of the patient. Pathological responses will be extracted from official medical records after surgery. Pathologists will not be aware of trial participation or group allocation.

#### Immunological response

In a recent study cyclic fasting during chemotherapy showed to downregulate peripheral blood immunosuppressive myeloid cells while increasing activated/cytotoxic cells (21). Thus, we plan to perform a multicolor flow cytometry 7 days after the administration of chemotherapy during the active trial period at 1 week, 7 weeks and 13 weeks. As the immunological changes are dependent on the day CHT is given, time points will be adjusted +/- 1 week depending on the days CHT is administered (e.g. in case of delayed CHT or public holidays). The blood samples will be stored in X-VIVO-medium with 10% DMSO (1 x 10^7^ cells/mL) at -80°C. Peripheral blood mononuclear cells (PBMCs) will be isolated from venous whole blood of the patients by gradient centrifugation. 10 ml blood will be separated by Ficoll using Leukosep tubes (Greiner) after lysis of erythrocytes (RBC lysis solution, Qiagen). The detection of leukocyte surface markers will be performed by using fluorochrome conjugated antibodies specific for CD3, CD8, CD14, CD15, CD25, CD56, CD69, HLA-DR, PD-L1 and PD1. Monocytes will be indicated by CD14 expression, PMN-MDSCs by CD15 expression, M-MDSCs by CD14 expression but HLA-DR negativity, PD-L1 positive immunosuppressive monocytes by CD14 and PD-L1 expression, T cells by CD3 expression and cytolytic NK cells by CD16 and CD56^dim^ expression of CD3 negative cells (21). To detect further immunological reactions, the cytokines CCL2, G-CSF, IL-6 and IL-8 will be quantified by ELISA (R&D Systems).

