Analyses will be performed as (1) modified intention-to-treat (ITT) population including all patients randomized who have at least received the first chemotherapy cycle. Patients will be analyzed in the group they were randomized to; (2) per-protocol (PP) sets, including all patients who have at least completed one/two/three or all chemotherapy cycles without major protocol violations. Safety will only be assessed in the per-protocol subset. Subgroup analyses will be performed by tumor type and type of CHT regime for groups with an adequately high number of participants. Furthermore, the parameters will be displayed graphically, and appropriate descriptive statistics will be employed. The significance level will be bilaterally set at 5%. 95% confidence intervals will be reported where appropriate. Due to the exploratory nature of secondary outcomes, no adjustments will be made for multiple testing.

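### The printed antibody panel omits CD16, which the next sentence needs to define cytolytic NK cells; the two should be reconciled before samples are stained

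*Protocol article*

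**What the plan says.** The Immunological response section (Methods, Secondary outcomes) states the assay, the panel and the population definitions in turn.

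- Assay: "we plan to perform a multicolor flow cytometry 7 days after the administration of chemotherapy during the active trial period". The section gives weeks 1, 7 and 13. Table 1 footnote 2 adds an assessment on the day of enrolment.
- Panel: surface markers are detected with "fluorochrome conjugated antibodies specific for CD3, CD8, CD14, CD15, CD25, CD56, CD69, HLA-DR, PD-L1 and PD1". No wording marks the list as a selection or as examples.
- Definitions, in the next sentence: "Monocytes will be indicated by CD14 expression, PMN-MDSCs by CD15 expression, M-MDSCs by CD14 expression but HLA-DR negativity", followed by PD-L1 positive monocytes, T cells and finally "cytolytic NK cells by CD16 and CD56"dim expression on CD3-negative cells.

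For the analysis, the Statistical analysis section says that "a list of immunological and metabolic parameters will be compared between both groups using the Mann-Whitney-U test". It also says: "Due to the exploratory nature of secondary outcomes, no adjustments will be made for multiple testing".

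**The concern.** A population can be gated only on markers that have been stained. The NK-cell definition requires CD16, and the article names no CD16 reagent. Someone who stained from the printed list would produce data to which the printed definition could not be applied.

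At stake is one named population. The section's rationale is a shift away from immunosuppressive myeloid cells and towards activated or cytotoxic cells, and cytolytic NK cells are the only population in the definition sentence that is labelled as cytotoxic. If the gap came to light only after staining, the population would have to be dropped or redefined with data in hand. That would sit badly with the statement under Detection bias that outcomes are fixed in advance.

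**Working it through.** No sample size, power or event figure bears on this point, so there is no plan figure to reproduce. The check is a set comparison: for each named population, take the markers its definition needs and remove those in the printed panel.

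**Inputs**, both from the Immunological response section: the ten-marker panel and the six population definitions.

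| Population | Markers needed | Needed but not in panel |
|---|---|---|
| Monocytes | CD14 | none |
| PMN-MDSCs | CD15 | none |
| M-MDSCs | CD14, HLA-DR | none |
| PD-L1 positive monocytes | CD14, PD-L1 | none |
| T cells | CD3 | none |
| Cytolytic NK cells | CD3, CD16, CD56 | **CD16** |

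Five of six definitions can be applied with the listed antibodies; one cannot.

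**Is CD16 supplied elsewhere?** The marker appears nowhere else in the article. The section's other assay is an ELISA for four cytokines, which does not gate cells. Appendix A, which is not shown, is cited under Body weight changes and safety for laboratory values; the Immunological response section does not refer to it for the panel.

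**What can still be measured?** Without the CD16 requirement, the definition becomes CD3-negative and CD56dim. Both markers are in the panel. Removing one required marker can only widen a set, so this group contains every cell that meets the full definition and possibly others. It is a usable NK-cell measure but a less specific one. The documents give nothing from which to estimate how far the two groups differ.

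**The reverse comparison.** CD8, CD25, CD69 and PD1 are in the panel but appear in none of the six definitions. This is not an error, but it shows that panel and definitions do not match one to one as printed.

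**Time points affected.** Enrolment (Table 1 footnote 2) plus weeks 1, 7 and 13 makes four, each with the same gap if the same panel is used.

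**The case against.** The strongest reply is that this is a slip in a printed list and not a fault in the laboratory work. The definition names CD16 outright, which suggests that the investigators mean to stain for it. The article condenses a fuller protocol (version 4.0, cited in the Ethics statement) that is not shown, and a reagent list is the kind of detail such a document may hold correctly. This is plausible and cannot be excluded. It does not remove the discrepancy, because the article states both the panel and the definitions and they disagree in adjacent sentences. That is a conflict in what is stated, not detail left to another document.

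The second reply is that little depends on it, and this largely stands. The Statistical analysis section treats the immune measures as one list of parameters without singling out NK cells. The secondary outcomes are declared exploratory. The Ethics statement lets patients decline the additional blood draws for mononuclear cells and stay in the trial. All four myeloid populations can be gated with the listed markers, so the wider immune hypothesis does not depend on CD16.

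A reader might infer more than the documents support:

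- That NK cells cannot be measured at all. They can, as CD3-negative CD56dim cells; only the definition as printed fails.
- That CD16 will not be stained. The article shows only that it is not listed.
- That storage at -80°C guarantees time to correct the panel. The article does not say when staining takes place or whether it is batched, so samples already stained may be beyond correction.

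**Conclusion.** The discrepancy is real but minor. If samples are stained as listed, one of six named populations, cytolytic NK cells, cannot be identified as defined at any of the four immune time points. This rests on reading the printed panel as complete, which its wording supports, and on the actual laboratory panel matching it, which the article cannot show. If CD16 is in the working panel, the matter reduces to a correction of the text.

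The primary fatigue comparison, the sample size and the other five populations are untouched. It would be wrong to infer that the immune component as a whole is compromised. Severity is low; the reason to act is that a stated measurement rule should be settled before the data exist.

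**What to change.** Before staining, and for any samples not yet stained, bring the panel and the definition into agreement in one of two ways:

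1. Add an anti-CD16 antibody to the panel and keep the definition. This costs one antibody and a check that it fits the existing panel; the article does not describe the cytometer configuration, so whether a channel is free must be confirmed locally. If CD16 is already stained, only the printed list needs correcting.
2. Keep the panel and redefine the population in advance as CD3-negative CD56dim cells, deleting CD16 from the definition. This is a one-line change; its cost is a less specific definition.

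Neither route needs extra blood or any change to the analysis. If some samples have already been stained without CD16, record that and state which definition applies to which samples before the arms are compared.
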